##### Child psychological symptoms

Externalising and internalising problem behaviours of the child will be assessed through parent- and teacher-ratings on the Conners’ Parent/Teacher Rating Scales-Revised: Long (CPRS-R:L [62]/CTRS-R:L [103]). We will use the subscales DSM-IV Inattentive Symptoms, DSM-IV Hyperactivity-Impulsive Symptoms, Oppositional, Anxious-Shy, Social problems and the Emotional Lability Index, resulting in questionnaires containing 44 (CPRS) and 37 items (CTRS). Items are scored on a 4-point rating scale ranging from 0 (*not true at all*) to 3 (*very much true*) with higher scores reflecting more symptoms. Both forms of the American version have a good internal consistency for all named subscales (Cronbach’s α coefficient ranging from .80 to .94) except the Emotional Lability Index, which is sufficient (Cronbach’s α coefficient ranging from .72 to .80) [103].

Symptoms of ASD will be assessed with the Social Responsiveness Scale (SRS) [104, 105] rated by parent and teacher. The 65 items can be organised into five subscales (i.e. Social Awareness, Social Cognition, Social Communication, Social Motivation, and Restricted Interests and Repetitive Behaviour) and two DSM-5 subscales (i.e. Social Communication and Interaction, and Restricted Interests and Repetitive Behaviour). Items are rated on a 4-point rating scale ranging from 1 (*not true*) to 4 (*almost always true*) with higher scores reflecting less social responsiveness. The Dutch version has a good internal consistency for both the parent- and teacher-form with Cronbach’s α coefficients of .92 and higher [106].

Brooding will be assessed using the self-report subscale of the Ruminative Response Scale (RRS; items reformulated by the authors for children from age 8) [107, 108]. Items are scored on a 4-point rating scale ranging from 1 (*almost never*) to 4 (*almost always*) with higher scores reflecting more brooding in response to sadness. The internal consistency of the American Brooding subscale is good (α = .80) when administered to adolescents [109].

##### Child well-being

We will use parents report on their child’s quality of life using the 11-item KIDSCREEN-10 [110]. Items are scored on a 5-point rating scale ranging from 1 (*never*) to 5 (*always*) with higher scores reflecting a higher health related quality of life. The internal consistency based on ten items is adequate (α = .78) [111].

##### Child mindfulness

Mindfulness skills will be assessed using self-report on the Child and Adolescent Mindfulness Measure (CAMM) [112, 113]. The CAMM consists of ten items that are scored on a 5-point rating scale ranging from 0 (*never true*) to 4 (*always true*) with lower scores reflecting better mindfulness skills. Internal consistency for the Dutch version was reasonable when administered to children (α = .71) and good for adolescents (α = .80) [112].

#### Secondary outcome measures for parents

##### Self-rated parental self-control

Adult versions of the self-control measures for children will be administered to parents. The BRIEF-A [114] is a 75-item self-report questionnaire comparable to the child version in rating scale and structure, but with slightly different subscales (i.e. Inhibit, Shift, Emotional Control, Self-Monitor, Initiate, Working Memory, Plan/Organise, Task Monitor and Organisation of Materials). The Dutch version shows a good internal consistency for the global executive composite score and both indexes (Cronbach’s α coefficient ranging from .92 to .96) and sufficient internal consistency for all subscales [114].

##### Computerised tasks of parental self-control

The parents’ version of the Stop Signal task and the Probabilistic Reversal Learning task will be identical to those described for children. The Stop Signal task shows an adequate test-retest reliability when administered to adults without a DSM-IV diagnosis in the past year (*r* = .65 for the SSRT) [115]. The Probabilistic Reversal Learning task shows adequate results when administered to adults with schizophrenia (ICC ranging from .49 to .68) [116].

As the Temporal Discounting task that will be used for children is not appropriate for use in adults, a hypothetical Temporal Discounting task will be administered to the parents. Participants make a series of choices regarding fictional amounts of money (rewards), ranging between one and hundred euros, available now versus after a specified delay interval (i.e. one month, one year, five years, ten years). Instructions are presented on the screen and are identical to those used by R. M. Hurst, H. O. Kepley, M. K. McCalla and M. K. Livermore [117]. For each trial, two variable rewards are presented in a random order, to increase the likelihood that the decisions are based on the amount in the individual trial and not on the previous trial. The participant’s score on the different delay intervals is the reward value where they switch between taking the delayed reward to taking the immediate one. The hypothetically Temporal Discounting task is widely used in various studies [97] and shows good internal consistency (α = .89) when administered to adults with and without self-reported ADHD [117]. Neurocognitive test instructions to parents can be found in Additional file 1.

##### Parental psychological symptoms

Symptoms of ADHD will be assessed using self-report on the Dutch version of the ADHD DSM-IV rating scale [118], which consists of 26 items concerning behaviour in the last two weeks (23 items) and childhood (three items). The latter three items are useful for estimating ADHD diagnosis, as onset of ADHD symptoms needs to be before the age of twelve according to the DSM-5. Items are scored on a 4-point rating scale ranging from 0 (*never or seldom*) to 3 (*very often*) with higher scores indicating more ADHD traits. The internal consistency is high for the Inattentiveness dimension (α = .83) and adequate for both the Hyperactivity (α = .75) and Impulsivity dimension (α = .72) [118].

Symptoms of ASD will be assessed using the self-rated 10-item Short Autism-Spectrum Quotient (AQ-10) [119, 120]. Each item is rated on a 4-point rating scale (1 = *definitely agree*, 2 = *slightly agree*, 3 = *slightly disagree*, 4 = *definitely disagree*) with higher scores indicating more symptoms of ASD. The internal consistency is good for the English 10-item version (α > .85) [120].

Symptoms of depression, anxiety and stress will be assessed using the self-rated 21-item Depression Anxiety Stress Scale (DASS-21) [121, 122] rated on a 4-point rating scale ranging from 0 (*did not apply to me at all*) to 3 (*applied to me very much of most of the time*). Higher scores reflect more symptoms of depression, anxiety and/or stress. All subscales of the Dutch version show a good internal consistency with Cronbach’s α coefficient ranging from .85 to .94 for students and a clinical sample of adults with an anxiety disorder and/or depression [122].

Brooding will be assessed using the Brooding subscale of the self-rated RRS [107, 108] containing five items that are rated on a 4-point rating scale ranging from 1 (*almost never*) to 4 (*almost always*). Higher scores indicate more brooding in response to sadness. The internal consistency of the Dutch Brooding subscale is sufficient (α = .78) when administered to adults [108].

##### Parental well-being

Quality of life will be assessed using the self-rated 5-item World Health Organization-Five Well-Being Index (WHO-5) [123]. Each item is scored on a 6-point rating scale ranging from 5 (*all the time*) to 0 (*not at all*). Higher scores reflect higher psychological well-being. The WHO-5 shows an adequate validity as an outcome measure in clinical controlled trials, sensitive for assessing change [124].

Emotional, psychological and social well-being will be assessed using self-report on the 14-item Mental Health Continuum-Short Form (MHC-SF) [125]. Each item is scored on a 6-point rating scale ranging from 0 (*never*) to 5 (*every day*) with higher scores indicating more positive mental health. The Dutch version shows high internal consistency for the total MHC-SF score (α = .89) and the two subscales Emotional and Psychological Well-Being (both α = .83), and adequate for the third subscale Social Well-Being (α = .74) [125].

##### Mindful parenting

We will use self-ratings on the 31-item Interpersonal Mindfulness in Parenting scale (IM-P) [126, 127] assessing 1) Listening with Full Attention; 2) Compassion for the Child; 3) Non-judgmental Acceptance of Parental Functioning; 4) Emotional Nonreactivity in Parenting; 5) Emotional Awareness of the Child and 6) Emotional Awareness of Self. Items are scored on a 5-point rating scale (1 = *never true*, 2 = *rarely true*, 3 = *sometimes true*, 4 = *often true*, 5 = *always true*) with higher scores reflecting more mindful parenting. The Dutch version of the IM-P shows a good internal consistency based on 29 items (α = .89) [126].

#### Tertiary measures for children

##### Self-rated

We will use the 8-item subscale Body Awareness of the Body Experience Questionnaire for Children (BEQC) as a tertiary measure, which shows an adequate internal consistency for the Dutch version (α = .71) [128]. Sensory-processing sensitivity will be assessed using the 12-item Highly Sensitive Child Scale (HSCS). The HSCS shows an adequate internal consistency (α = .79) [129]. For children aged eleven and older we will use the 24-item Inventory of Callous-Unemotional Traits (ICU) assessing uncaring, callousness and unemotional traits. The Dutch version shows a good internal consistency (α = .89) [130]. Self-compassion will be assessed by using one item per subscale of the Self-Compassion Scale [131] with the highest factor loading [132]. This resulted in six exploratory items which were reformulated by the authors for children. Mind-wandering will be assessed using an exploratory questionnaire (items developed by JB for this study, 2015) containing three items (e.g. “When you are busy with schoolwork, a task or a chore, do you notice that you are daydreaming?”).

##### Parent-rated

The 18-item DSM-IV-based Strengths and Weakness of ADHD Symptoms and Normal Behaviour (SWAN) [133] will be used to assess ADHD traits (inattentiveness and hyperactivity-impulsivity). The Dutch version of the SWAN shows a good internal consistency (α > .87) when administered to parents (α = .88) [134] and will be included as it provides good resolution across the full range of continuous ADHD traits, thereby potentially providing additional information to the Conners’ Rating Scales [135]. Neuroticism, as a covariate for the HSCS, will be assessed by administering the 5-item Big Five questionnaire [136]. Sleeping habits will be assessed using the 5-item Sleep Questionnaire used in standard clinical care assessing problems with sleeping in, sleeping through and total amount of sleep compared to children of the same age.

##### Teacher-rated

The above described 18-item SWAN [133] will be administered to teachers, also showing a high internal consistency for the Dutch version (α = .91) [134].

##### Tasks

Reading speed and accuracy will be assessed with the Dutch One Minute Reading Test; a test of word decoding, in which children are instructed to read as many words from a list as possible within one minute. The test shows a good test-retest reliability with high correlations ranging from .80 to .92 [137].

#### Tertiary measures for parents

##### Self-rated

The 12-item Highly Sensitive Person Scale (HSPS) will be administered to parents assessing sensory-processing sensitivity, showing a good internal consistency (α = .89) when administered to adults [136]. Neuroticism, as a covariate for the HSPS, will be assessed by administering the 5-item Big Five questionnaire [136]. For the six subscales of the Self-Compassion Scale, the item that correlates the most with the total scale will be selected to create a 6-item questionnaire to explore self-compassion [132].

### Qualitative research

Qualitative interviews with families and mindfulness teachers will be conducted after the family MBI, with the aim to capture the richness and heterogeneity of experiences of families with ADHD potentially not tapped by the quantitative assessments, and to facilitate adaptations to the MYmind protocol based on participant and mindfulness teacher experience. Purposive sampling will be used to include a subset of families with different backgrounds, age groups, gender and drop-outs will also be interviewed. Data will be generated until saturation is reached. The interviews are semi-structured using a topic guide focusing on two main topics: 1) facilitators and barriers to participating in family MBI training; and 2) effects of family MBI on parent, child and parent-child interactions. Interviews will be conducted separately with parent, child and mindfulness teachers. All interviews will be audio recorded, transcribed verbatim and analysed in the Atlas.ti software using Grounded Theory [138]. Analysis will be performed by a team of researchers to ensure no data get lost. Essential aspects of qualitative research concerning relevant participant selection, appropriate data collection methods, comprehensive data collection process and data analysis will be followed [139].

### Biological assessments

Studying (epi)genetic factors alongside environmental factors in relation to family MBI can help understand the biological basis of family MBI. Five saliva samples will be drawn from children for DNA and RNA isolation and assessment of biomarkers: one OG-500 DNA at baseline for genotyping of DNA; one Oragene OG-575 DNA at baseline and one at end of treatment for methylomic profiling of CpG DNA sequences; and one Oragene RE-100 RNA at baseline and one at end of treatment for profiling of transcriptomics (mRNA), microRNA expression and epigenomic profiling. The collection of saliva during end of treatment will be scheduled during the same time of the day as the collection at baseline within participants to account for hormonal fluctuations. Children will be asked to refrain from food and drinks (except water) and cigarettes thirty minutes before collection. Samples will be processed under barcode in a validated and well-controlled pipeline designed to process samples for clinical use. The material of biological nature will be stored at − 20 or − 80 °C (as appropriate; RE-100 RNA vials to be stored at − 80 °C to minimise any RNA degradation). Data will be stored in an automated, validated laboratory information system (Labvantage: www.labvantage.com/).

### Procedure and treatment allocation

Recruitment will take place within the outpatient clinics of Karakter through screening by the researchers of currently treated patients or through referral by the psychiatrist. In addition, recruitment will take place via media advertisement (e.g. flyers and website). In case there are no contra-indications (i.e. exclusion criteria, crisis situation or family does not want to be approached for scientific research), families will be contacted by phone to inform them about the study and to establish whether they meet the inclusion criteria. Next, information letters will be sent to parent and child via e-mail. Families will have a minimum of two weeks to consider participation. Families willing to participate will then be sent forms of informed consent in the post: parental consent of child participation, parental consent of own participation, child consent (age > =12 years) of own participation. Participants not referred by Karakter will also give consent to request medical data from the institute/clinician who diagnosed ADHD. The participants will be randomised after completion of the informed consent forms. In case families withdraw consent before the baseline assessments, randomisation will be undone and participants can be replaced, in order not to let non-participants imbalance the treatment groups for the primary analyses. School teachers and general practitioners of included participants will be informed about the study via telephone, email and/or postal letter. The school teachers will be requested not to ask the family about treatment allocation to keep them ‘blinded’. Likewise, the participants will be requested not to speak about treatment allocation to the school teachers.

Assessments will take place at baseline (T0), end of treatment (T1), two (T2) and six (T3) months after end of treatment. For the family MBI condition, T0 will be scheduled in the two weeks prior to the start of the intervention and T1 in the two weeks after the 8th session of the MYmind training. The booster session will be followed by the first follow-up assessments (T2) which will be two months after T1 and the second follow-up assessments (T3) will be scheduled half a year after T1. Intervals between assessments will be kept similar for the family MBI and CAU condition. For baseline, end of treatment and 6-month follow-up assessments, participants will be invited to a location of Karakter. Assessments will be conducted by a researcher or research assistant. Participants will be asked to interrupt ADHD medication intake 48 h prior to these assessments. For the 2-month follow-up assessments, both parent and child will receive an invitation to complete questionnaires online (not at Karakter). School teachers will be asked to complete all questionnaires online at baseline, end of treatment and 2-month follow-up. See Table 1 for which assessments for children will be taken at which time points and Table 2 for assessments for parents and time points. Further, see Fig. 1 for a flowchart on recruitment and the study procedure.

**Table 1 Tab1:** Assessments for children and time points

Assessments for children	Time points			
*Descriptives*				
Demographics	T0			
WISC-III (Vocabulary and Block Design)	T0			
Investigator-rated K-SADS-PL	T0			
Self-rated PDS	T0			T3
*Primary outcome measure*				
*Parent-rated child self-control*				
BRIEF-P	T0	T1	T2	T3
*Secondary outcome measures*				
*Teacher-rated self-control*				
BRIEF-T	T0	T1	T2	
*Computerised tasks of self-control*	T0	T1		T3
*Psychological symptoms*				
Parent-rated CPRS-L:R (subscales DSM-IV inattentive symptoms, DSM-IV hyperactivity-impulsive symptoms, oppositional, anxious-shy, social problems, emotional lability index)	T0	T1	T2	T3
Teacher-rated CTRS-L:R (subscales DSM-IV inattentive symptoms, DSM-IV hyperactivity-impulsive symptoms, oppositional, anxious-shy, social problems, emotional lability index)	T0	T1	T2	
Parent-rated SRS	T0	T1		T3
Teacher-rated SRS	T0	T1		
Self-rated RRS (Brooding)	T0	T1		T3
*Well-being*				
Parent-rated KIDSCREEN-11	T0	T1		T3
*Mindfulness*				
Self-rated CAMM	T0	T1	T2	T3
*Tertiary measures*				
*Self-rated*				
BEQC	T0	T1		T3
HSCP	T0			
ICU (ages 11+)	T0	T1		
Self-compassion (exploratory items)	T0	T1		T3
Mind-wandering (exploratory items)	T0	T1	T2	T3
*Parent-rated*				
SWAN (optional)	T0	T1		T3
Neuroticism (covariate for HSCP)	T0			
Sleeping habits	T0	T1		T3
*Teacher-rated*				
SWAN	T0	T1		
*Tasks*				
One Minute Reading Test	T0	T1		T3
*Saliva collection*	T0	T1		

T0 baseline, T1 end of treatment, T2 2-month follow-up, and T3 6-month follow-up, WISC-III Wechsler Child Intelligence Scale-Third Edition, K-SADS-P Schedule for Affective Disorders and Schizophrenia for School-Age Children-Present and Lifetime Version, PDS Pubertal Development Scale, BRIEF-P Behaviour Rating Inventory of Executive Function-Parent form, BRIEF-T Behaviour Rating Inventory of Executive Function-Teacher form, CPRS-L:R Conners’ Parent Rating Scales-Revised: Long, CTRS-L:R Conners’ Teacher Rating Scales-Revised: Long, SRS=Social Responsiveness Scale, RRS = Ruminative Response Scale, CAMM = Child and Adolescent Mindfulness Measure, BEQC=Body Experience Questionnaire for Children, HSCP=Highly Sensitive Child Scale, ICU=Inventory of Callous-Unemotional Traits, and SWAN=Strengths and Weakness of ADHD Symptoms and Normal Behaviour

**Table 2 Tab2:** Assessments for parents and time points

Assessments for parents	Time points			
*Descriptives*				
Demographics	T0			
WAIS-III (Vocabulary and Block Design)	T0			
Self-rated K10	T0			
Investigator-rated MINI	T0			
*Secondary outcome measures*				
*Self-rated self-control*				
BRIEF-A	T0	T1	T2	T3
*Computerised tasks of self-control*	T0	T1		T3
*Psychological symptoms*				
Self-rated ADHD DSM-IV rating scale	T0	T1	T2	T3
Self-rated AQ-10	T0	T1		T3
Self-rated DASS-21	T0	T1		T3
Self-rated RRS (Brooding)	T0	T1		T3
*Well-being*				
Self-rated WHO-5	T0	T1		T3
Self-rated MHC-SF	T0	T1		T3
*Mindful parenting*				
Self-rated IM-P	T0	T1	T2	T3
*Tertiary measures*				
Self-rated HSPS	T0			
Self-rated neuroticism (covariate for HSPS)	T0			
Self-rated self-compassion (exploratory items)	T0	T1		T3

*Note*. T0 baseline, T1 end of treatment, T2 2-month follow-up, and T3 6-month follow-up, WAIS-III=Wechsler Adult Intelligence Scale-Third Edition, K10 = 10-item Kessler Psychological Distress Scale, MINI = Mini-International Neuropsychiatric Interview, BRIEF-A = Behaviour Rating Inventory of Executive Function-Adult version, AQ-10 = 10-item Short Autism-Spectrum Quotient, RRS = Ruminative Response Scale, WHO-5 = 5-item World Health Organization-Five Well-Being Index, MHC-SF = Mental Health Continuum-Short Form, DASS-21 = 21-item Depression Anxiety Stress Scale, IM-P=Interpersonal Mindfulness in Parenting Scale, and HSPS=Highly Sensitive Person Scale

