#### Eligibility criteria

We will include families who meet the following criteria: a) child is 8–16 years old and in the third grade of primary school or higher; b) child has a primary diagnosis of ADHD according to the Diagnostic and Statistical Manual of Mental Disorders (DSM-IV or DSM-5) system [60, 61] and confirmed by a structured interview (see Assessments section); c) child receives CAU for ADHD and has remaining ADHD symptoms (average score > 1.0 on the investigator-rated DSM-5 items from the Conners’ ADHD rating scale [62]); d) ADHD medication dose of child is stable, at least two weeks prior to baseline, or an informed decision is made on not taking ADHD medication; e) at least one parent is willing to participate. Exclusion criteria are a) psychosis, bipolar illness, active suicidality, untreated posttraumatic stress disorder or substance use disorder of the child that impedes functioning; b) psychosis, bipolar disorder, active suicidality, untreated posttraumatic stress disorder or substance use disorder of the parent that impedes functioning; c) child and/or participating parents have an estimated Intelligence Quotient (IQ) < 80; d) child and/or participating parents do not have adequate mastery of Dutch language; e) child and/or participating parents have participated in an > = 8-week mindfulness programme in the past year or ever in a Mindful Parenting training; f) child or parents participate in another intervention study.

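### Randomisation precedes the baseline visit and the time of disclosure is not stated, so the parent-rated ANCOVA covariate and the diagnostic confirmation can be influenced by knowledge of the arm

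*Protocol article*

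**What the plan says.** Under Procedure and treatment allocation, the protocol article states: "The participants will be randomised after completion of the informed consent forms". The rule on early withdrawal confirms that this comes before baseline: "In case families withdraw consent before the baseline assessments, randomisation will be undone and participants can be replaced". The Randomisation section also places allocation directly after consent.

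The timing of baseline depends on the arm: "For the family MBI condition, T0 will be scheduled in the two weeks prior to the start of the intervention". Intervals between assessments are to be kept similar in the CAU arm.

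On knowledge of allocation, the article protects only the teachers. They are asked not to enquire, and "the participants will be requested not to speak about treatment allocation to the school teachers". So families know their arm at some point, but no date is given. Nothing is said about blinding of parents or of the person who conducts T0.

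Two items collected at T0 matter here:

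- **BRIEF-P.** It is the primary outcome, rated by a parent (Primary outcome measure; Table 1). Its baseline value is the covariate in the primary ANCOVA (Statistical analyses).
- **K-SADS-PL.** Inclusion criterion b requires a primary ADHD diagnosis "confirmed by a structured interview (see Assessments section". The Descriptives section says that this interview is given to a parent, and Table 1 lists "Investigator-rated K-SADS-PL" at T0.

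**The concern.** ANCOVA gives an unbiased treatment estimate in a randomised trial when allocation cannot affect the covariate. Measuring the covariate before allocation, or before anyone knows the allocation, guarantees this. Here the covariate is a subjective rating by a parent who is also a recipient of the intervention. It is taken after allocation and, in the MBI arm, shortly before the course starts.

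Higher BRIEF scores mean more problems. If parents who know that the course is coming rate the child worse at T0 than they otherwise would, ANCOVA treats this as real baseline severity and credits MBI with too much improvement. If hope or relief makes them rate the child better, a real effect is hidden. The strong baseline correlation that allows a sample of 42 per arm also carries most of any such distortion into the estimate.

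The K-SADS-PL raises the same question in a lesser form, because the information that confirms an inclusion criterion comes from the same parent after allocation.

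**Working it through.** **Inputs from the Power calculation section:** d = 0.4, two-sided α = .05, power 80%, r = .76, D = 1 − .76² = .4224 (given as .42), 42 per arm, and 50 per arm after attrition of about 15%.

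**The plan's own figure.** The two-sample t-test needs 99.08 per arm, rounded up to 100. Then 100 × .42 = 42, and 42/0.85 = 49.4, rounded up to 50. The stated sample size reproduces, and this point does not affect it.

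**Assumption.** The documents give no size for an allocation-driven shift in the T0 rating. Call it *s*, in SD units, occurring in the MBI arm only. The range examined is 0 to 0.3. T0 and T1 are taken to have equal SDs, so the regression slope equals r.

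**Scenario A: shift at T0 only.**

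- Size of bias in the adjusted difference = r × *s* = .76*s*. It favours MBI if T0 is rated worse in that arm, and goes against MBI if T0 is rated better.
- SE of the adjusted difference = √(2 × .4224/42) = 0.142 SD.
- Two-sided rejection rate with no true effect = Φ(−1.96 + bias/SE) + Φ(−1.96 − bias/SE).
- Power when the bias works against MBI = Φ((0.4 − bias)/SE − 1.96).

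| *s* (assumed) | Bias (SD) | Share of d = 0.4 | Type I error | Power if against MBI |
|---|---|---|---|---|
| 0 | 0 | 0% | 5.0% | 80% |
| 0.1 | 0.076 | 19% | 8.3% | 63% |
| 0.2 | 0.152 | 38% | 18.8% | 42% |
| 0.3 | 0.228 | 57% | 36.2% | 23% |

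A simulation of the ANCOVA (10,000 runs, 42 per arm) gave biases of 0.077, 0.152 and 0.230 SD in size, and type I error of 8.1%, 18.1% and 34.3%.

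**Scenario B: the same shift persists to T1.** The outcome moves by *s* and the covariate adjustment removes .76*s*. The net bias is *s* − .76*s* = .24*s*, with the opposite sign to scenario A. For *s* = 0.1, 0.2 and 0.3 this is 0.024, 0.048 and 0.072 SD, with type I error of about 5.3%, 6.3% and 8.0%.

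**Would the planned baseline comparison reveal it?** Not reliably. The SE of a raw baseline difference is √(2/42) = 0.218 SD, so even *s* = 0.3 is only 0.3/0.218 = 1.4 standard errors. It could not be told apart from chance imbalance, and ANCOVA would adjust for it as if it were one.

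**The case against.** **Disclosure before T0 is not documented.** A reader might infer that parents and assessors definitely know the arm at T0. The inference is strong, because MBI visits are booked relative to the course and families must plan for eight weekly sessions. But the article gives no disclosure date, and the flowchart is not available in the text reviewed. Withholding the arm until T0 is complete would be compatible with everything stated. This part of the objection stands: the defect is missing protection, and unblinding at T0 is not established.

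**The bias is conditional.** A reader might infer that the primary estimate is biased. The documents support only that it can be. Neither the size nor the sign of *s* is known, and scenario B is no less documented than scenario A. The 8% to 36% range belongs to one scenario.

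**Eligibility is not generally decided after allocation.** A reader might infer that the K10, "Investigator-rated MINI" and IQ testing at T0 also decide eligibility, and that families will be removed with their arm known. The documents do not support this. Exclusion criteria are considered before families are approached, and inclusion criteria are checked by phone before consent. The IQ subtests are used only where no valid result exists. The K10 and MINI are listed as descriptives and are not named as the test for any exclusion criterion. No text says that families failing a criterion at T0 are removed, and the rule for undoing randomisation covers only withdrawal of consent. What remains is the K-SADS-PL, which criterion b does require through a structured interview.

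**The outcome rating is open anyway.** Parents know the arm at T1 whatever the order, and the teacher-rated BRIEF gives a partial check on rater effects. Both are true. Reordering does not cure the open T1 rating, but it removes a separate and avoidable route to bias. The teacher rating is secondary and does not protect the primary analysis.

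**Conclusion.** The point holds in conditional form. Allocation before T0 is stated. That the parent-rated covariate and the parent-informed diagnostic confirmation are collected after allocation follows directly, and no protection is described. The primary estimate can therefore be biased in either direction.

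For assumed shifts of 0.1 to 0.3 SD, the bias is 0.08 to 0.23 SD if the shift is confined to T0. It is 0.02 to 0.07 SD, with the opposite sign, if the shift persists equally to T1. It is zero if there is no shift. These figures rest on r = .76, 42 per arm, equal SDs and a shift in one arm only. The size of the shift itself is an assumption. The point is worth acting on because prevention is cheap, while a baseline rating already given with the arm known cannot be repaired by analysis.

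**What to change.** Change the order to consent, then T0 (at least the BRIEF-P and the K-SADS-PL confirmation), then randomisation. If forming the course groups requires earlier allocation, keep the current order but state that the arm is withheld from the family and from the person conducting T0 until T0 is complete. In either case, state in the protocol when families are told. If withholding is already the practice, one sentence saying so closes the point.

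No extra visits, staff or participants are needed, and the sample size is unchanged. The cost is practical. Families get shorter notice of their arm and must hold the course dates provisionally. If randomisation itself moves after T0, groups of about 5–8 children and the parallel parent groups are finalised later, within the two-week window before the course. The change cannot help families who have already passed T0. For them, report the order of disclosure and T0 alongside the primary result.
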